## Abstract

**Background:**

Asthma that is poorly controlled and undertreated can progress to more severe disease that is associated with high levels of unscheduled care that requires high-cost therapy, leading to a significant health economic burden. The identification and appropriate referral to a specialist asthma service is also often delayed by several months or years because of poor recognition and understanding of symptom severity. Current severe asthma services may take several months to provide a comprehensive multidisciplinary assessment, often necessitating multiple hospital visits and costing up to £5000 per patient.

**Objective:**

This study aims to evaluate whether a new service model could identify poorly controlled and potentially severe asthma much earlier in the patient pathway, and then compare clinical outcomes between this new care model with standard care.

**Methods:**

Modern Innovative Solutions to Improve Outcomes in (MISSION) Severe Asthma is a novel service model developed by asthma specialists from Portsmouth and Southampton severe asthma services. MISSION Severe Asthma identified patients with poorly controlled disease from general practice databases who had not been under secondary outpatient care in the last 12 months or who were not known to secondary care. In 1- or 2-stop assessments, a thorough review of diagnosis, disease phenotype, and control is undertaken, and clinical outcomes collected at baseline.

**Results:**

A variety of clinical outcomes will be collected to assess the service model. The results will be reported in February 2020.

**Conclusions:**

This protocol outlines a mixed methods study to assess the impact on disease control, unscheduled health care usage, and quality of life in patients seen in the MISSION clinic compared with a closely matched cohort who declined to attend.

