## Methods

### Study Design

A mixed methods observational study evaluating the new service, comparing outcomes before and after the intervention, and including a control arm of patients not exposed to, but eligible for, the new intervention is included. This will include analyses of the MISSION participants (attending both the RAAC and SAAC clinics), patients from the existing asthma service (from outpatient severe asthma clinics), and data from patients on GP records who were eligible to attend MISSION but did not (primary care patients). Finally, qualitative methods will be used to explore participant and health care professionals’ views on MISSION. Multimedia Appendix 1 summarizes the participants journey and the different populations under study.

The MISSION Severe Asthma project has not been designed as a randomized controlled trial (RCT) but designed to evaluate a novel service model (the intervention) in participants with uncontrolled and potentially severe asthma, to assess whether it is deliverable and acceptable by participants and health care professionals, and to explore the barriers that would need to be addressed before a larger RCT.

A patient advisor reviewed all patient-facing documentation for the study and will give advice and feedback on the structure of the qualitative interviews.

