#### Secondary Outcome Measures for Modern Innovative Solutions to Improve Outcomes in Rapid Access Asthma Clinic Patients and Primary Care Patients

Prescription of SABAs during last 6 months at baseline and 6 months.Exacerbation rates (defined as deterioration in symptoms requiring ≥30 mg prednisolone or equivalent for ≥3 days) during the last 6 months at baseline and 6 months.ED attendances, OOH contacts, and hospital admissions during the last 6 months at baseline and 6 months.Inhaled steroid doses and usage.Number of patients having measurement of FEV1÷FVC as a proxy for asthma control and severity.The sensitivity and specificity of the PRIMIS (Primary Care Information Services, University of Nottingham) Asthma Audit Tool in identifying the patients compared with gold standard specialist assessment and interrogation of primary care records.

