### Screening and Enrollment

#### Quantitative

All patients from the RAACs and all primary care patients will be approached for consent to use their anonymized data from the MISSION clinics or from GP records for research purposes. No extra data for research purposes will be collected for the quantitative analysis from patients at MISSION assessments, asthma outpatient clinics, or GPs.

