#### Analysis of Endpoints

The analyses will compare the study outcomes between the 4 study groups.

The primary outcome is exacerbation frequency. This outcome will be analyzed using ANCOVA, with the outcome variable being exacerbation frequency in the second 6-month period and the exacerbation rate in the first 6-month period treated as the covariate. Owing to the likely skewed distribution of the exacerbation frequency, it may be necessary to perform a log transformation of the outcome before analysis. Comparisons will be made overall between the 3 groups, and specifically between the MISSION group and each of the other 2 groups.

The analysis of secondary outcomes measured on a categorical scale during the second 6-month period will be compared between groups using Fisher exact test. Continuous variables will be compared between groups using analysis of variance, if found to be normally distributed, or the Kruskal-Wallis test, if not found to be normal.

Comparisons between groups will also be made accounting for the values during the first time period. ANCOVA will be used for continuous variables, whereas logistic regression will be used for binary outcomes.

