### Primary Care Patients

All patients identified by the GP search but who did not attend the MISSION clinics will be approached for the study to maximize the chance of getting the same number of participants to the number who consents from the MISSION group.

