### Outpatient Severe Asthma Patients

The severe asthma outpatient clinic at Portsmouth Hospitals NHS Trust sees 16 new referrals per month. The sample will be matched to the same as the number of patients attending the SAACs, that is, 20 patients. All new referrals to the asthma clinic who meet the inclusion criteria will be included until the sample size is reached.

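### The controls are described as closely matched, but they are all consenting invitees who did not attend, and the primary model adjusts only for prior exacerbations, so some self-selection may remain

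*Protocol article*

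**What the plan says.** The Conclusions paragraph of the abstract presents the comparison as MISSION patients "compared with a closely matched cohort who declined to attend".

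The body builds the control group differently. Under Eligibility Criteria, primary care patients are those flagged by the record search and invited to the RAAC who did not attend. Under Results, Primary Care Patients: "All patients identified by the GP search but who did not attend the MISSION clinics will be approached for the study". Under Screening and Enrollment: "All patients from the RAACs and all primary care patients will be approached for consent to use their anonymized data". Matching is otherwise mentioned only for a different group, the hospital outpatients, and there it concerns only how many are taken: "The sample will be matched to the same as the number of patients attending the SAACs, that is, 20 patients".

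For the primary outcome, Analysis of Endpoints specifies ANCOVA on second-period exacerbation frequency with "the exacerbation rate in the first 6-month period treated as the covariate". Sample Size uses the same one-covariate model. Study Design states openly that the study is observational and not randomized.

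**The concern.** A reader of the abstract will assume that controls were selected to resemble attenders on several characteristics. They were not. They are whoever was left after patients decided whether to attend, and then whether to consent.

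People who accept a Saturday clinic invitation may differ from those who do not in smoking, treatment level, adherence, severity or past use of urgent care. Any such difference that affects later exacerbations, and is not carried by the prior exacerbation count, goes into the estimated effect of the service. RAAC versus non-attenders is one of the primary objectives and is the comparison on which the study was powered, so the main result is affected.

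**Working it through.** **1. The label against the construction.** The abstract claims matching and says the cohort declined. The sections on eligibility, enrolment and primary care patients describe no matching variables, ratio or procedure at patient level. Declining is also narrower than not attending. The Results section on RAAC and SAAC patients gives 125 booked and 84 attended, so 125 − 84 = 41 booked and did not come.

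**2. How selective attendance was.** That section gives 460 patients meeting the criteria, all invited: 84/460 = 18.3%, leaving 376 non-attenders. The Quantitative paragraph of the Results gives 369 identified and approached: 84/369 = 22.8%, leaving 285. The two counts need reconciling. Attendance is a minority choice on either.

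**3. The plan's own sample size.** Inputs from Sample Size: SD 1.30, correlation 0.5, means 1.29 and 0.65 (difference 0.64), ratio 3:1, 5% significance (taken as two-sided), 90% power.
- Adjusted SD = 1.30 × √(1 − 0.5²) = 1.126.
- This gives 44 and 132, as stated (power 90.4%). The sample size arithmetic is sound and is not at issue.

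**4. What one baseline covariate removes.** With equal SDs in the two periods, the ANCOVA slope equals the correlation, 0.5. If the groups differ by a stable amount D in both periods and the service does nothing, the adjusted difference is D − 0.5 × D = 0.5 × D. Half remains. For an assumed D of 0.3, the residue is 0.15, and 0.15/0.64 = 23% of the planned effect.

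**5. The same rule for an unadjusted risk factor.** The prevalences and rate ratios are assumptions. The non-attender mean is 1.29, and the last column is the residue divided by 1.29.

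| Rate ratio | Prevalence, non-attenders vs attenders | Crude ratio of means | Gap before adjustment | Left after halving | Apparent reduction |
|---|---|---|---|---|---|
| 2 | 60% vs 30% | 1.3/1.6 = 0.81 | 0.242 | 0.121 | about 9% |
| 1.5 | 60% vs 40% | 1.2/1.3 = 0.92 | 0.099 | 0.050 | about 4% |

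**6. Effect on the test.** At 44 and 132, the SE of the adjusted difference is 1.126 × √(1/44 + 1/132) = 0.196. With no true effect, a residual bias of 0.15 (0.15/0.196 = 0.77 SE) makes the two-sided 5% test reject about 12% of the time.

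Steps 4 to 6 are on the untransformed scale. The plan allows a log transformation, so they are approximate.

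**7. Whether better adjustment is possible.** The secondary outcomes for RAAC and primary care patients include SABA prescriptions and ED, OOH and hospital contacts at baseline, and "Inhaled steroid doses and usage". Table 1 ticks medication history, health care usage and smoking status for the same two groups. Apart from each outcome's own first-period value, none of these enters a primary or secondary model.

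**The case against.** The groups are not arbitrary. Controls came from the same search, met the same criteria and received the same invitation. The criteria cover inhaled steroid dose, exacerbations, urgent contacts, SABA use and FEV1, and the primary model adjusts for the baseline value of the outcome. The abstract's phrase may be loose shorthand for this, and the article does not hide that the study is non-randomized. An analysis plan that is not shown could add sensitivity analyses.

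Much of this stands: selection through those routes is reduced. But a patient needed only one or more of the criteria, so one may qualify on steroid dose alone and another on repeated exacerbations. The article also fixes the primary model instead of deferring it. The later sentence on accounting for first-period values follows the secondary outcomes and adds only each outcome's own baseline.

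Two stronger readings are tempting and are not supported.
- A reader might take the crude ratio of 0.81 to mean that a service with no effect would appear to cut exacerbations by 19%. That ignores the planned baseline adjustment. Under the same assumptions about 9% is left.
- A reader might infer that the bias flatters the service. Nothing in the article shows this. If the more symptomatic patients came forward, the bias would run against it.

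**Conclusion.** The concern holds in a limited form. The abstract's description of the control cohort is wrong on the article's own account: no patients are matched, and not all controls declined. The primary model leaves out recorded baseline differences that attendance may have selected on.

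The size can only be illustrated. Under r = 0.5, equal SDs and a stable difference, half of any gap survives: 0.15 of an assumed 0.3 (23% of the planned 0.64), or apparent reductions of about 9% and 4% in the two assumed risk-factor examples. The article gives no figure for actual imbalance, and the direction is unknown. It therefore does not support saying that the groups are incomparable or that a positive result would be an artefact. It supports saying that the comparison is less protected than the abstract states and that better protection is available from data already planned.

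**What to change.** - **Label.** In the abstract, describe the comparator as eligible invited patients who did not attend. Drop the references to matching and declining.
- **Primary model, RAAC versus non-attenders.** Alongside baseline exacerbations, prespecify a short covariate set: baseline SABA inhalers, baseline inhaled steroid dose, baseline ED/OOH contacts and admissions, age and sex. Add smoking only if it is taken from GP records made before the invitation, because attenders had smoking reviewed at the clinic and it may be recorded differently in the two groups.
- **Alternative.** Use propensity-score overlap weights on the same variables, and state that they target a somewhat different population from covariate adjustment.
- **Reporting.** Show a baseline balance table for attenders and non-attenders. Word the conclusion as an adjusted association, because measured covariates cannot capture motivation or adherence.

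**Cost.** The extra analysis is modest, and most of the variables are already due for extraction in both groups. Some GP entries will be missing or unevenly recorded. The added terms use a few degrees of freedom with only about 44 MISSION patients, so the list should stay short.

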**International Registered Report Identifier (IRRID):**

DERR1-10.2196/9585

## Introduction

### Background and Rationale

#### The Burden of Disease

Asthma affects 5.4 million patients in the United Kingdom with the majority of costs (nearly 80%) relating to treating poorly controlled asthma, amounting to over £1 billion per annum as a direct cost and an indirect cost to society (time off work and lost productivity) of £6 billion. In the past year, the Wessex Region has seen over 1800 emergency adult hospital admissions because of asthma (over 300 more than expected based on the national average), costing over £2.1 million to the local health authority.

Asthma UK highlights that over half of the people with asthma suffer debilitating symptoms despite being prescribed treatment [1]. Poorly controlled disease leads to exacerbations necessitating unscheduled care and high-cost medications while impairing a patient’s quality of life and increasing the risk of premature death. In 2009, there were 1131 deaths because of asthma in the United Kingdom, triggering a Department of Health–commissioned National Audit of Asthma Deaths [2]. Reviews of asthma deaths have confirmed that those with the most severe, frequently exacerbating disease are at greatest risk of death. The Outcome Strategy for Chronic Obstructive Pulmonary Disease and Asthma recognized this huge burden on both patients and the National Health Service (NHS) and outlined the political commitment to improve asthma control and reduce asthma-related emergency health care needs and deaths [3]. Asthma UK also highlighted the need to improve the quality of life of people with asthma by improving access to services, reducing inequalities in care, and ensuring a high standard of care. It is accepted that the proactive clinical review of people with asthma improves clinical outcomes and the majority with poorly controlled asthma can achieve good control. The recent publication “NHS five-year forward view” identifies the traditional separation of primary and secondary care being a barrier to the integrated care that patients with chronic disease require [4].

#### The Unmet Need

The Specialised Services Pathway for Severe Asthma recognizes the burden of uncontrolled disease ordinarily amenable to antiinflammatory medications and the progression to longer term “severe” disease, necessitating high-cost therapies (e.g. bronchial thermoplasty) [5]. The identification and appropriate referral to a specialist asthma service is often delayed by several months or years because of poor recognition and understanding of symptom severity.

Current severe asthma services may take several months to provide a comprehensive multidisciplinary assessment often necessitating multiple hospital visits and costing up to £5000 per patient. The report “Fighting for Breath” highlighted these issues with service delivery recommending that referral pathways to severe asthma services should be improved [6].

#### Description of Clinical Intervention and Treatment

Modern Innovative Solutions to Improve Outcomes in (MISSION) Severe Asthma is a novel service model pilot that took place in June and July 2014. MISSION was developed by asthma specialists from Portsmouth and Southampton asthma services.

The MISSION concept involved a “carousel clinic” which brings together all the assessments and investigations a patient requires into one clinic—the patient moved around each assessment or “investigation station” in a serial fashion. This allowed the research team to efficiently gather all the data required for both staff and the patient. This severe asthma patient journey was mapped and opportunities for improvement were identified such as earlier diagnosis by active case finding of at-risk patients, followed by a swift multidisciplinary assessment which meant patients could be seen sooner and assessed more effectively. Patients attending standard outpatient services undergo basic lung function, chest x-ray, and medical review. They are then referred for other tests or specialist opinions as required at different time-points

MISSION Severe Asthma identified patients with poorly controlled disease from general practice (GP) databases who had not been under secondary outpatient care in the last 12 months or who were not known to secondary care. The patients were then invited to Rapid Access Asthma Clinics (RAACs) for assessment at their GP surgery on a Saturday, at a time convenient for them. The clinics were held on Saturdays at a time better suited to the needs of asthma patients, many of whom are working or studying full-time.

The RAAC delivered a comprehensive asthma review including assessments of allergic status, airway inflammation, education, self-management planning, and smoking cessation leading to a written personalized 1-year asthma management plan for their GP providing clear treatment recommendations for those with uncontrolled but treatable asthma (see Figure 1). Treatment recommendations were in line with current asthma guidelines.

**Figure figure1:**
[figure not shown]
MISSION Severe Asthma Rapid Access Asthma Clinic flow chart. MISSION: Modern Innovative Solutions to Improve Outcomes.

At the end of the RAAC, a multidisciplinary team (MDT) meeting was held and treatment plans were discussed. The possible outcomes for patients included increasing or decreasing medication, referral for research study, referral to other medical teams, or a need for further assessment as the patient has potentially severe and uncontrolled asthma. Patients with potentially severe and uncontrolled asthma were invited for a more detailed multidisciplinary specialist assessment at a Severe Asthma Assessment Clinic (SAAC) again on a Saturday, held at Queen Alexandra Hospital.

MISSION SAAC included multidisciplinary assessment respiratory specialists, dieticians, physiotherapists, ear, nose, and throat (ENT) consultants, physiologists, psychologists, and pharmacists. Computed tomography (CT) scanning of the chest and sinus as well as flexible nasendoscopy to assess for sinus change and nasal polyps was available on that day. Patients saw the appropriate specialists based on the clinical history from the RAAC and a medical assessment on arrival to the SAAC. This ensured full lung function, inhaler technique, and medical exam for all patients, and physiotherapy, dietician, ENT, CT chest or sinus were performed where needed (see Figure 2). Representatives from Allergy UK also attended the clinic and provided advice and support to patients who were interested.

**Figure figure2:**
[figure not shown]
MISSION Severe Asthma Rapid Access Asthma Clinic flow chart. CT: computed tomography; ENT: ear, nose, and throat; FeNO: fractional exhaled nitric oxide; MDT: multidisciplinary team; MISSION: Modern Innovative Solutions to Improve Outcomes; PFT: pulmonary function test.

At the end of the clinic, a full MDT meeting was held to discuss each case. Patients and their GP received a detailed letter with all the test results and treatment changes as well as plans for follow-up. Follow-up referrals were made to specialists as needed, and treatment changes were made on the day of the clinic visit with support from the pharmacy for new treatment prescriptions.

In summary, the difference of the MISSION clinic from standard care was in 2 areas: First the active case finding of patients who are not already known to secondary care but are potentially uncontrolled. The second is the model of the clinic. Patients seen at the RAAC only will undergo more extensive testing and review of their asthma than primary care can provide and will have their comorbidities identified, asthma phenotyped, and treatment changes made appropriately.

#### Rationale for Study and Potential Impact

MISSION is a new and novel way of delivering highly specialized asthma care and has the potential to change the way asthma care is delivered across the United Kingdom as well as services for other long-term health conditions. The MISSION model is the first model of this type, and this study aimed to evaluate its success and compare the MISSION service with current care delivery. This will be done in several different ways. The study is a mixed methods evaluation of the new service comparing outcomes before and after the MISSION clinic using retrospective data analysis and prospective qualitative interviews. A control arm of patients not exposed to, but eligible for, the new MISSION clinic will also be included.

### Objectives

Using quantitative and qualitative methods, our objective is to explore the impact of the MISSION service on clinical outcomes and patient experience. Using quantitative methods, we will (1) retrospectively analyze data collected as part of routine clinical care from all patients attending MISSION e.g. asthma control, medication usage and technique, exacerbations, comorbidities, allergies, and investigations (blood tests, radiological imaging, and nasendoscopy) and (2) retrospectively compare the assessment of comorbidities, investigations, and treatments between MISSION SAAC patients and standard outpatient care.

